#### Other outcomes

Other study parameters include SAEs, physical examination, and clinical laboratory tests. At every study visit, blood samples will be drawn. This will be done according to the schedule of assessments at weeks 0, 4, 8, 12, 16, 20, and 24 (Table 4). Laboratory testing will be done locally. The following tests will be standardly performed: haemoglobin (Hb), haematocrit (ht), absolute neutrophil count, white blood cell count, platelet count, prothrombin time, INR, ALT, AST, GGT, albumin, alkaline phosphatase (ALP), bilirubin (direct and indirect), creatinine (eGFR), IgG, and urinalysis: pregnancy tests in women of childbearing potential. All patients will undergo transient elastography by a Fibroscan at screening or at week 4, and at week 24 for assessment of liver fibrosis.

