**Table 4 Tab4:**
[figure not shown]
The schedule of enrolment, interventions, and assessments in the Standard Protocol Items: Recommendations for Interventional Trials (SPIRIT) figure

*AIH* autoimmune hepatitis, *AZA* azathioprine, *LF* last known follow-up, *MMF* mycophenolate mofetil

^a^Done in week 4 if not available in participating centre ^b^optional ^c^in women of childbearing potential ^d^retrospective collection of data

It is expected that patients will continue to have regular visits outside of the study context. In this natural cohort of patients, data regarding the continuation of study medication, experienced side effects and persisting remission will be collected 52 weeks after the end of the study visit (T76) and at the last known follow-up. This data will be collected retrospectively and outside of the study context.

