#### Patient-reported outcomes

Questionnaires will be filled in at screening, 4, 16, and 24 weeks. Quality of life will be assessed using the SF-36, and the Work Productivity and Activity Impairment Questionnaire: General Health V2.0 questionnaires [34, 35]. AIH-related complaints will be assessed using the Liver Disease Symptom Index 2.0 questionnaire [36].

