#### Sample size calculation

Since most evidence from the standard AIH treatment comes from clinical trials performed several decades ago, we have used the more recent budesonide trial from Manns et al. to determine efficacy rate of prednisolone and azathioprine in AIH [37]. In this study, 38.8% of patients reached normalisation of AST and ALT levels after 6 months of prednisolone and azathioprine treatment. When it comes to treatment with MMF, only limited data is available. The only prospective study showed that 88% of patients reached normalisation of ALT, AST, and IgG within 1-12 months, while at three months 70% reached normalisation [28]. Retrospective studies show lower response rates for MMF (Table 1). Based on available literature, we hypothesise that instead of a 70% response rate at three months, 70% at 6 months with MMF is feasible in the intervention group. A sample size of 32 patients per group will results in 1-beta of 0.80 with a two-sided alfa of 0.05 significance level to detect the difference in means of −36.2% (75.0% versus 38.8%). Taken into account a fallout rate of 10%, the total number in each group will therefore be 35 patients.

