### Analysis

#### Statistical analysis

Descriptive analysis will be performed for all baseline and demographic data. Normally distributed variables will be noted as mean with standard deviation (S.D.), and not-normally distributed variables will be noted as median with range or inter-quartile range (IQR) if stated. Categorical data will be noted as numbers and percentages of the total.

All randomised patients are evaluated for primary and secondary endpoints at 24 weeks. The primary analysis is based on intention-to-treat (ITT) principles. ITT analyses will be used for all clinical outcome variables. Every patient who has received at least one dose of study medication will be included in the ITT analysis. A per-protocol analysis will also be performed in patients who received >80% of the study medication. When deemed necessary, missing data will be dealt with accordingly with supportive statistical analyses (e.g. imputation or appropriate models) to assess the potential effects. These methods will be addressed in the final manuscript. Treatment effects will be analysed by comparing the difference in proportion with biochemical remission at 24 weeks between both groups. Values will be compared using Student’s *t* test, Mann-Whitney *U* test, Pearson test, Wilcoxon’s rank sum test, Wilcoxon signed-rank test, chi-square test or Fischer’s exact test, as appropriate. Time to remission will be tested and compared using a Kaplan-Meier survival analysis with log-rank test. Time to remission will be censored at 24 weeks. Significance of statistical differences is attributed to p <0.05. All statistical analyses will be performed with Statistical Package for Social Sciences (SPSS), version 22.0.

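### The single pre-drug liver stiffness scan may fall before or after four weeks of prednisolone, and the named tests adjust for neither baseline nor scan timing (minor, secondary outcomes only)

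*Protocol article*

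**What the plan says.** **Scan timing.** Under Other outcomes: "All patients will undergo transient elastography by a Fibroscan at screening or at week 4, and at week 24". A footnote to Table 4 reads "Done in week 4 if not available in participating centre". This fits a timing that depends on the centre, but the table is not shown, so the row to which the footnote belongs cannot be confirmed.

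**Outcome.** Secondary outcomes lists change in liver stiffness, change in MELD and its components, change in albumin and change in SF-36. None of these entries names a baseline visit.

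**Treatment timeline.** Under Study design and recruitment and in Tables 2 and 3, prednisolone falls from 40 or 60 mg/day in week 1 to 20 mg/day in week 4. Patients may enter at any point in those four weeks. The randomised drug starts at 4 weeks.

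**Other measurements.** Bloods are scheduled at both week 0 and week 4 (Other outcomes). For quality of life: "Questionnaires will be filled in at screening, 4, 16, and 24 weeks".

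**Tests.** The Statistical analysis section begins its list with "Values will be compared using Student" and continues with rank, chi-square and exact tests, to be chosen as appropriate. None has a baseline term. Models are mentioned only for missing data.

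**The concern.** Only one scan is planned before the randomised drug. Taken at screening, it gives a change to week 24 that spans the early steroid phase. Taken at week 4, it gives a change that starts after that phase. Any effect of those weeks on stiffness enters some change scores and not others, and it has nothing to do with MMF versus azathioprine. An unadjusted comparison treats it as noise and also leaves chance baseline differences uncorrected.

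With about 32 evaluable patients per arm, detectable differences in a continuous secondary outcome are already large. Avoidable variance makes them larger.

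**Working it through.** **The plan's own figure.** No power is stated for any change outcome. The only calculation is for the binary primary endpoint: "A sample size of 32 patients per group will results in 1-beta of 0.80", "with a two-sided alfa of 0.05 significance level", for rates of "75.0% versus 38.8"%. Exact enumeration at 32 per group gives 80.1% power with Fisher's test, so the figure reproduces. The allowance for 10% fallout (32 × 1.1 = 35.2; 32 / 0.9 = 35.6) is close to the stated 35. These figures supply n = 32 per arm below and are otherwise unaffected.

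**Step 1: change score versus ANCOVA.** Let r be the correlation between baseline and week 24, and assume equal variances SD² at the two times. The documents give no r, so a range is used.

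- Change score variance: 2(1 − r) SD²
- ANCOVA variance: (1 − r²) SD²
- Ratio: (1 − r²) / [2(1 − r)] = (1 + r)/2

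Detectable differences are in SD units at 80% power, two-sided 0.05, 32 per arm, from the noncentral t distribution with one degree of freedom spent on the covariate. The last column is ANCOVA power at the effect where the change score has 80%.

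| r (assumed) | Variance ratio | Detectable, change score | Detectable, ANCOVA | ANCOVA power |
|---|---|---|---|---|
| 0.3 | 0.65 | 0.84 | 0.69 | 93% |
| 0.5 | 0.75 | 0.71 | 0.62 | 89% |
| 0.7 | 0.85 | 0.55 | 0.51 | 85% |
| 0.9 | 0.95 | 0.32 | 0.31 | 81% |

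**Step 2: unequal variances.** With baseline SD s₀ and week-24 SD s₁, the change-score variance is s₀² + s₁² − 2r s₀s₁ and the ANCOVA variance is s₁²(1 − r²). The difference is s₀² − 2r s₀s₁ + r²s₁² = (s₀ − r s₁)², which is never negative. The percentages in Step 1 need equal variances. The direction does not, apart from the small cost in degrees of freedom.

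**Step 3: mixed scan timing.** Suppose a fraction f of patients is scanned at week 4 and mean stiffness differs by D (in SD) between the two times. Both are assumptions. If timing is independent of arm, the change score gains variance f(1 − f)D².

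- f = 0.25, D = 0.5: 0.25 × 0.75 × 0.25 = 0.047. At r = 0.7 the change-score variance is 2 × 0.3 = 0.60, so this adds 0.047/0.60 = 8%.
- f = 0.5, D = 1: 0.5 × 0.5 × 1 = 0.25, which adds 0.25/0.60 = 42%.

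A simulation of the second case (4,000 runs, 32 per arm, r = 0.7) gave these standard errors of the treatment difference:

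| Analysis | Uniform timing | Mixed timing |
|---|---|---|
| Change score | 0.191 | 0.235 |
| ANCOVA on the scan | 0.179 | 0.198 |
| ANCOVA plus timing indicator | 0.179 | 0.183 |

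Mean bias was about zero throughout. Adjusting for the scan alone recovers part of the loss; the timing indicator recovers most of the rest. By formula, the fully adjusted analysis has 0.51/(0.60 + 0.25) = 0.60 of the change-score variance, about 40% less.

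**Step 4: cost.** One covariate inflates ANCOVA variance by about 1 + 1/(2 × 32 − 4) = 1.017. In the worst case, r = 0 against a comparison of week-24 values alone, the detectable difference rises from 0.711 to 0.718 SD, about 1%.

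**The case against.** The strongest reply is that the baseline visit and covariates for a secondary outcome usually belong in the statistical analysis plan, which is not shown, and that this article condenses a fuller protocol. The list of tests says as appropriate and assigns none to stiffness. That stands as a limit: the plan may already deal with this. But the either/or scan timing is stated, and so is a list of methods that contains no adjusted one. The point concerns those statements.

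A second reply is that randomisation is stratified by centre and cirrhosis, so centre-driven timing would tend to balance. This supports the absence of expected bias. It does not guarantee balance: 14 centres × 2 cirrhosis levels gives up to 28 strata, or 70/28 = 2.5 patients each, fewer than the smallest block of 4. Nor does balance remove the extra variance from an unadjusted change score.

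Third, the percentages in Step 1 hold in any trial and do not measure the mixed timing. That is correct. The timing part depends on f and D, which the documents do not give.

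Three stronger readings are tempting and are not supported:

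- **All change outcomes have a screening-or-week-4 baseline.** The documents say this only of elastography. Bloods and questionnaires have both values scheduled. The gap there is an unnamed baseline, and screening values may also fall at varying times after prednisolone began.
- **The comparison is biased.** Nothing links scan timing to arm.
- **Adjusting every outcome for its week-4 value is free.** Patients can be randomised before week 4 in an open-label trial, so a week-4 SF-36 score may be given with knowledge of the arm. For stiffness, only one pre-drug scan is planned, so the last pre-drug value is itself the mixed value.

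**Conclusion.** The point holds for liver stiffness: the baseline scan is allowed at two times that differ by up to four weeks of prednisolone, and the methods named take no account of it. For MELD and its components, albumin and SF-36 it holds in a weaker form: no baseline is named and the listed tests do not adjust.

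The consequence is lost precision. ANCOVA has 35% to 5% less variance than a change-score test as r goes from 0.3 to 0.9, assuming equal variances. For stiffness, mixed timing comes on top: 8% to 42% more change-score variance in the two illustrative cases at r = 0.7. All values of r, f and D are assumptions.

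The issue is minor. Only secondary outcomes are affected; the primary endpoint and the sample size are not.

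**What to change.** Before the analysis, state the following:

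- **Liver stiffness:** analyse the week-24 value, on the log scale if skewed, by ANCOVA on arm, the pre-drug scan, an indicator for screening versus week-4 scan, and cirrhosis.
- **MELD and its components, albumin:** name one baseline visit for all patients and analyse the week-24 value by ANCOVA on arm, that baseline and cirrhosis.
- **SF-36:** do the same, with a score obtained before randomisation as the baseline.

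The cost is one degree of freedom for the baseline, a second for scan timing where it applies, and one for cirrhosis. The scans, bloods and questionnaires are already scheduled; the date of each scan and of each SF-36 relative to randomisation has to be available. The Trial status section reports 66 of 70 patients randomised, so a single common scan visit is largely out of reach and the remedy lies in the analysis.

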**Table 4 Tab4:**
[figure not shown]
The schedule of enrolment, interventions, and assessments in the Standard Protocol Items: Recommendations for Interventional Trials (SPIRIT) figure

*AIH* autoimmune hepatitis, *AZA* azathioprine, *LF* last known follow-up, *MMF* mycophenolate mofetil

^a^Done in week 4 if not available in participating centre ^b^optional ^c^in women of childbearing potential ^d^retrospective collection of data

It is expected that patients will continue to have regular visits outside of the study context. In this natural cohort of patients, data regarding the continuation of study medication, experienced side effects and persisting remission will be collected 52 weeks after the end of the study visit (T76) and at the last known follow-up. This data will be collected retrospectively and outside of the study context.

#### Patient-reported outcomes

Questionnaires will be filled in at screening, 4, 16, and 24 weeks. Quality of life will be assessed using the SF-36, and the Work Productivity and Activity Impairment Questionnaire: General Health V2.0 questionnaires [34, 35]. AIH-related complaints will be assessed using the Liver Disease Symptom Index 2.0 questionnaire [36].

#### Sample size calculation

Since most evidence from the standard AIH treatment comes from clinical trials performed several decades ago, we have used the more recent budesonide trial from Manns et al. to determine efficacy rate of prednisolone and azathioprine in AIH [37]. In this study, 38.8% of patients reached normalisation of AST and ALT levels after 6 months of prednisolone and azathioprine treatment. When it comes to treatment with MMF, only limited data is available. The only prospective study showed that 88% of patients reached normalisation of ALT, AST, and IgG within 1-12 months, while at three months 70% reached normalisation [28]. Retrospective studies show lower response rates for MMF (Table 1). Based on available literature, we hypothesise that instead of a 70% response rate at three months, 70% at 6 months with MMF is feasible in the intervention group. A sample size of 32 patients per group will results in 1-beta of 0.80 with a two-sided alfa of 0.05 significance level to detect the difference in means of −36.2% (75.0% versus 38.8%). Taken into account a fallout rate of 10%, the total number in each group will therefore be 35 patients.

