## Background

Autoimmune hepatitis (AIH) is a severe chronic liver disease associated with cirrhosis and liver failure [1, 2]. AIH is a rare disease, its prevalence is estimated at 17–23 cases per 100,000 inhabitants in Europe [3, 4]. It is characterised by a spectrum of clinical manifestations and may lead to complications of progressive liver disease, including cirrhosis, portal hypertension, and hepatocellular carcinoma. Untreated AIH has very poor outcomes and is usually fatal [2, 5].

Immunosuppressive therapy consisting of azathioprine and corticosteroids has emerged as the mainstay of active autoimmune hepatitis management. This has greatly improved survival rates [6–8]. Normalisation of transaminases is achieved in 65–70% after 6 months, irrespective of prednisone dosage [9]. However, almost 20% of patients experience adverse effects (AEs) with azathioprine treatment, such as nausea, vomiting, arthralgia, skin rash and fever, which necessitate cessation of treatment in approximately 15% of patients in the first year [10, 11]. In recent years, mycophenolate mofetil (MMF) has been explored as an alternative option to standard care in AIH treatment. Most studies focused on the use of MMF as second-line rescue therapy in AIH patients who were either intolerant or refractory to azathioprine. MMF seems to be generally better tolerated than azathioprine. Several retrospective studies reported remission rates, which varied from 25 to 100% (Table 1) [12–25]. This has led to recommendations in the European Association of the Study of the Liver (EASL) guidelines and the European Society for Paediatric Gastroenterology Hepatology and Nutrition (ESPGHAN) position statement of MMF as second-line treatment for patients who do not respond to or do not tolerate azathioprine [26, 27]. Meanwhile, MMF has aroused interest as an alternative option for AIH induction therapy. A prospective uncontrolled study explored the efficacy of MMF in treatment-naive AIH patients [28]. Fifty-nine treatment-naive AIH patients received open-label MMF at a final dose of 1.5–2 g daily combined with a standardised prednisolone tapering scheme. Eighty-eight per cent of patients had an initial clinical and biochemical response with normalisation of serum aspartate transferase (AST), alanine transferase (ALT) and immunoglobulin gamma (IgG) levels. While the data on MMF in AIH patients are promising, randomised clinical trials are needed to generate high-quality evidence.

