### Outcomes

#### Primary outcome

The primary outcome is the percentage of patients in biochemical remission, defined as normalisation of serum ALT and IgG levels, per treatment group. This primary endpoint will be assessed at 24 weeks of treatment.

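### The stated 80% power rests on a 38.8% azathioprine rate that is not reconciled with the 65–70% in the protocol's own Background

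*Protocol article*

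**What the plan says.** All references are to the protocol article.

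- **Background.** The section introduces standard treatment: "Immunosuppressive therapy consisting of azathioprine and corticosteroids has emerged as the mainstay of active autoimmune hepatitis management". Two sentences later it gives the result: "Normalisation of transaminases is achieved in 65–70% after 6 months, irrespective of prednisone dosage".
- **Sample size calculation.** Most evidence on standard treatment is said to come from trials done decades ago, so the more recent budesonide trial supplies the control rate: "38.8% of patients reached normalisation of AST and ALT levels after 6 months of prednisolone and azathioprine treatment". The higher Background figure is not mentioned, and no range of control rates is given.
- **MMF rate.** The reasoning ends at "70% at 6 months with MMF is feasible in the intervention group", but the calculation uses "75.0% versus 38.8" (per cent).
- **Size and power.** "A sample size of 32 patients per group will results in 1-beta of 0.80", with a "two-sided alfa of 0.05 significance level". A 10% fallout allowance brings this to 35 per group.
- **Primary outcome.** The endpoint is "biochemical remission, defined as normalisation of serum ALT and IgG levels, per treatment group", assessed at 24 weeks.

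**The concern.** Read together, the two sections give control rates that differ by 26 to 31 points (65 − 38.8 = 26.2; 70 − 38.8 = 31.2). As the article presents them, both concern azathioprine plus a corticosteroid, about 6 months of treatment, and normal transaminases. The reason given for using the budesonide trial is its date. That explains the choice of source, but it does not say why the Background figure, written in the present tense as what standard therapy achieves, should not apply to this trial's control arm.

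The endpoint adds a second gap. The 38.8% is for AST and ALT without IgG. The prospective MMF data set against it are for ALT, AST and IgG. The primary outcome is ALT and IgG. No azathioprine rate for that combination appears anywhere in the article.

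What is at stake is how the result is read. With 32 to 35 patients per group, power depends strongly on the control rate. A reader who sees only 80% could give a non-significant result more weight than it can bear.

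**Working it through.** **Inputs.** Control 38.8%, MMF 75.0%, 32 per group, two-sided 0.05 (Sample size calculation). Control 65–70% (Background). Alternative MMF rates of 88% within 12 months and 93.8% at 6 months, from treatment-naive cohorts (Table 1). Control rates between 38.8% and 65% are my assumption, to show the range.

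**Method.** Exact power is the sum, over all pairs (i, j) of remission counts, of Bin(i; 32, p_C) × Bin(j; 32, p_M) for the pairs where the test gives p < 0.05. I use Fisher's exact test and the uncorrected chi-square test, since the Statistical analysis section allows either.

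**Step 1: the plan's own figure.** At 38.8% v 75.0% with 32 per group, Fisher power is 0.801 and chi-square power 0.866. The stated 0.80 therefore reproduces with Fisher's test. The arithmetic is not at fault.

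**Step 2: vary the control rate, with MMF held at the planned 75%.**

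| Control rate | Difference (points) | Fisher | Chi-square |
|---|---|---|---|
| 38.8% | 36.2 | 80% | 87% |
| 40% | 35 | 77% | 84% |
| 45% | 30 | 62% | 72% |
| 50% | 25 | 46% | 56% |
| 60% | 15 | 18% | 25% |
| 65% | 10 | 9% | 14% |

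The midpoint of 38.8% and 65% is (38.8 + 65)/2 = 51.9%. Power there is 40% (Fisher) or 50% (chi-square).

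**Step 3: let MMF exceed the plan.**

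| Control v MMF | Fisher | Chi-square |
|---|---|---|
| 55% v 88% | 80% | 87% |
| 60% v 88% | 66% | 76% |
| 65% v 88% | 50% | 60% |
| 65% v 93.8% | 77% | 86% |

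**Step 4: precision.** The approximate 95% CI half-width for the risk difference is 1.96 × √[(p_C(1 − p_C) + p_M(1 − p_M))/n]. At 65% v 75% with n = 32 this is 1.96 × √[(0.2275 + 0.1875)/32] = 0.223. At 38.8% v 75% it is 1.96 × √[(0.2375 + 0.1875)/32] = 0.226. The interval spans about 22 points either side of the estimate in both cases, so it conveys what the trial can exclude whichever control rate is true.

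**Related but separate.** If MMF is set to the 70% named in the text, power at 38.8% v 70% is 66% (Fisher) or 75% (chi-square). That inconsistency needs its own correction and is not used above.

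**The case against.** The strongest defence is that 38.8% was a reasoned choice. The article says why it preferred the budesonide trial, and its Discussion describes that trial as double-blind and randomised with 203 patients. The Background figure is one sentence with no design, population or dosing. This stands: the documents do not show that 38.8% is wrong. It does not remove the need to say why the higher figure was set aside. The Discussion also describes that trial's primary endpoint as excluding steroid-specific side effects. Whether the 38.8% carries that restriction cannot be settled from the article.

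Two stronger readings are tempting, and the documents support neither.

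- **That true power is about 5–15%.** This needs two conditions at once: a control rate of 65–70% on the primary endpoint, and MMF no better than 70–75%. The 65–70% is for transaminases only, and requiring normal IgG as well could lower it by an amount the article does not give. Table 1 also lists 88% and 93.8% for MMF in treatment-naive cohorts. Those cohorts are uncontrolled and the plan did not rely on rates that high, but they show that the low figures are not the only ones the article supports.
- **That the planned gain is impossible because 65 + 36.2 = 101.2%.** The 36.2 points were derived for a 38.8% control rate. Moving them unchanged to another control rate tests something the plan never claimed. Power falls gradually between the two rates, as Step 2 shows.

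It is also fair to say that a superiority trial need not state a rule against claiming similarity, and that confidence intervals are often left to the analysis plan. I do not count their absence as a fault.

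**Conclusion.** The concern holds as an unreconciled planning assumption. The calculation is correct for its inputs, but 80% holds only near 38.8% v 75%. With MMF at the planned 75%, Fisher power is already 62% at a 45% control rate and 46% at 50%, and it reaches 9% at the lower end of the Background range. At a 65% control rate, power near 80% needs MMF at about 94%, well above the 70–75% planned.

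These values assume 32 evaluable patients per group, an unadjusted two-sided comparison at 0.05, and control rates chosen to span the article's two figures. Because the control rate for ALT plus IgG is not given, the shortfall is conditional. What can be said firmly is that the article's own Background does not support a single unqualified 80%.

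**What to change.** - Reconcile the Background with the Sample size calculation: say why 38.8% is preferred to 65–70%, whether it carries the side-effect restriction described in the Discussion, and how the IgG requirement is expected to affect it.
- Restate the 80% as holding only near 38.8% v 75%, with a short table of power for control rates from 38.8% to 65%.
- Report the primary result as a risk difference with its 95% CI, so that a non-significant result is read against that precision.

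No change in enrolment is proposed; 66 of 70 patients had been randomised when the article was written. The cost is a few sentences and a small table. The downside is that the stated power will look less favourable.

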### Study design and recruitment

CAMARO is a phase IV, randomised (1:1), open-label, parallel-group, multicentre superiority trial in 70 patients with treatment-naive AIH. All patients with established AIH according to the simplified criteria for the diagnosis of AIH [32] and who are considered for induction therapy will be eligible for the study. Eligibility will be assessed at the screening visit (SV) and patients will start with prednisolone according to the treatment schedules in Tables 2 and 3. A patient may enter the study at any time point in the first 4 weeks, as long as the prednisone schedule has been used for induction therapy. After informed consent, patients will be randomised in a 1:1 ratio to one of the two treatment arms. At 4 weeks, patients will consequently start with either azathioprine or MMF in dosages exactly according to the schedule (Tables 2 and 3). Eight follow-up visits are scheduled at weeks 4, 8, 12, 16, 20, and 24. The week 24 visit is the end of the treatment visit. After that, patients can continue azathioprine or MMF as assigned, as maintenance therapy. A trial flowchart is shown in Fig. 1.

**Table 2 Tab2:** Treatment schedule for patients 40–80 kg

Week	Prednisolone (mg/day)	Azathioprine (mg/day)	MMF (mg/day)
1	40	-	-
2	30	-	-
3	25	-	-
4	20	-	-
5	15	50	1000
6	12,5	50	1000
7[contact]
9+10	7,5	100	2000
From week 11 onwards	5	100	2000

*MMF* mycophenolate mofetil, *mg* milligrams

**Table 3 Tab3:** Treatment schedule for patients >80 kg

Week	Prednisolone (mg/day)	Azathioprine (mg/day)	MMF (mg/day)
1	60	-	-
2	45	-	-
3	30	-	-
4	20	-	-
5	15	50	1000
6	12,5	50	1000
7[contact]
9+10	7,5	100	2000
From week 11 onwards	5	100	2000

*MMF* mycophenolate mofetil, *mg* milligrams

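### The sample size is calculated for 75.0% remission on MMF, but the stated hypothesis is 70%; at 70% the claimed 80% power is about 66% (Fisher) to 75% (chi-square)

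*Protocol article*

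**What the plan says.** All the figures are in the Sample size calculation section of the protocol article.

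- **Control rate.** It comes from the budesonide trial, in which "38.8% of patients reached normalisation of AST and ALT levels after 6 months of prednisolone and azathioprine treatment".
- **MMF rate, as argued.** The section cites a prospective study with 88% normalisation within 1 to 12 months and 70% at three months, and notes that retrospective studies found lower rates. It concludes that "70% at 6 months with MMF is feasible in the intervention group", and presents this as the hypothesis.
- **MMF rate, as calculated.** The next sentence reads "A sample size of 32 patients per group will results in 1-beta of 0.80 with a two-sided alfa of 0.05". It gives the difference to be detected as 36.2 points and the comparison as "75.0% versus 38.8" per cent.
- **Allowance for loss.** "Taken into account a fallout rate of 10%, the total number in each group will therefore be 35 patients".

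The Statistical analysis section lists both the chi-square test and Fisher's exact test, to be used as appropriate, and does not say which applies to the primary endpoint.

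**The concern.** Two consecutive sentences give different remission rates for the MMF arm. The first settles on 70%; the second powers the trial for 75.0%. The higher rate is not explained, and no study cited in the paragraph reports it. It is not a slip confined to one number: the printed difference of 36.2 equals 75.0 − 38.8, so 75.0% is the rate that entered the calculation.

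This is the article's only power statement for the primary endpoint of a superiority trial. If remission on MMF is 70%, as hypothesised, the trial has less than the stated power. A non-significant result would then be read against 80% power that the design does not have for that effect, and so would be taken as stronger evidence against MMF than it is. The Discussion says that randomised data on first-line MMF are lacking, which makes such a misreading more costly.

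**Working it through.** **Inputs**, from Sample size calculation unless noted:

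- two-sided α = 0.05; target power 0.80
- azathioprine rate 0.388
- MMF rate 0.75 (as calculated) or 0.70 (as hypothesised)
- 32 evaluable per group, 35 enrolled per group
- 1:1 allocation (Study design and recruitment)
- chi-square or Fisher's exact test (Statistical analysis)

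**Method.** Let X be the number in remission on MMF and Y the number on azathioprine, independent binomials with n per group. Exact power is the sum of P(X = i) × P(Y = j) over all pairs (i, j) for which the two-sided p-value is below 0.05. Chi-square here means Pearson's test without continuity correction.

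**Step 1: reproduce the plan's figure.** At 0.75 against 0.388, Fisher's test has power 77.7% with 31 per group and 80.1% with 32. So 32 is the smallest group size that reaches 80%, and the stated figure reproduces with Fisher's test. The continuity-corrected chi-square gives 80.0% at 32.

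The pooled-variance formula without correction is

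n = [1.96·√(2p̄(1−p̄)) + 0.8416·√(p₁(1−p₁) + p₂(1−p₂))]² / (p₁ − p₂)².

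With p₁ = 0.75, p₂ = 0.388 and p̄ = 0.569:

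n = (1.96 × 0.7003 + 0.8416 × 0.6519)² / 0.362² = 3.691 / 0.1310 = 28.2, that is 29 per group.

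**Step 2: put in the stated hypothesis.** With p₁ = 0.70 and p̄ = 0.544:

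n = (1.96 × 0.7044 + 0.8416 × 0.6689)² / 0.312² = 3.777 / 0.0973 = 38.8, that is 39 per group.

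**Step 3: exact power at both rates.**

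| Per group | MMF rate | Fisher | Chi-square |
|---|---|---|---|
| 32 | 75.0% | 80.1% | 86.6% |
| 32 | 70% | 65.7% | 74.7% |
| 35 (no loss) | 75.0% | 81.7% | 87.2% |
| 35 (no loss) | 70% | 66.0% | about 74% |

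On the same test, moving from 75.0% to 70% at 32 per group costs 80.1 − 65.7 = 14.4 points (Fisher) or 86.6 − 74.7 = 11.9 points (chi-square). Three more patients per group barely help, because exact power does not rise smoothly with n. The pooled normal approximation, which is smooth, gives 71.7% at 32 and 75.7% at 35, still below 80%.

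**Step 4: size needed for 80% at 70%.** With Fisher's test, 45 per group gives 79.2% and 46 gives 80.5%. With chi-square, 38 gives 79.4% and 39 gives 81.1%. The evaluable number needed is therefore 46 or 39 per group, against 32 planned.

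**Side check on the allowance for loss.** 35 × 0.9 = 31.5, and 32 / 0.9 = 35.6, which rounds up to 36. The 35 per group is short by a rounding step only, and nothing here depends on it.

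**The case against.** The calculation may be right and the sentence before it wrong. The 75.0% is given to one decimal with a matching difference, and as a power statement for that alternative it is correct. The article does not say which rate was meant. If 75.0% was intended, 80% power stands for that effect, and the fault is a wrong hypothesis sentence and an unsupported planning rate.

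That much stands, and the lower power figures should be read as power at 70%. It does not remove the problem: 70% is what the article says it hypothesises, and at 70% neither listed test reaches 80%.

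A second objection is that the range of 66% to 75% mixes a change of rate with a change of test, because the plan's 80% corresponds to Fisher's test. This is fair, and each test should be compared with its own figure at 75.0%, as in the table. The loss is about 12 to 14 points either way.

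Finally, recruitment is nearly complete, with 66 of 70 randomised according to Trial status, and neither the analysis nor the type I error is affected. That is a reason not to ask for more patients. It is no reason to leave the power statement uncorrected.

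**Conclusion.** The point holds: the sample size statement is wrong as written. It claims 80% power, but under the hypothesis in the preceding sentence (70% against 38.8%, two-sided 0.05, 32 evaluable per group) power is 65.7% with Fisher's test and 74.7% with the uncorrected chi-square test. The chance of missing the hypothesised effect is 34.3% or 25.3%, where 20% is implied. The shortfall remains with all 70 patients evaluable.

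The figures assume independent binomial outcomes and a control rate of exactly 38.8%, and they take the stated 70% as the hypothesis. The contradiction between the two rates does not depend on any of these assumptions.

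**What to change.** Correct the Sample size calculation section so that one planning rate is named as intended, and give a source for 75.0% if that rate is kept. Whichever was meant, state the power at both rates, for example:

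> With 32 evaluable patients per arm the trial has 80% power (Fisher's exact test) to detect 75.0% against 38.8%, and about 66% (Fisher) to 75% (chi-square) for 70% against 38.8%.

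Carry the same statement into the final report, so that a non-significant result is not read against 80% power for the 70% hypothesis.

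The cost is one corrected sentence and a less favourable power figure. No change in enrolment or analysis is asked for.
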